##### JOA Score^[17]^

2.8.1.2

Clinical symptoms and difficulty in performing tasks of daily living were evaluated according to the therapeutic effects evaluation standard of the Japanese Orthopedics Association (JOA) for lumbago. All scores before and 3 weeks after treatment were recorded and total scores calculated, in accordance with JOA's score for lumbago and leg pain severity.

##### **ODI**^[18]^

2.8.1.3

Prior to and 3 weeks following treatment, the Oswestry disability index (ODI) of each patient was recorded, principally referring to pain (degree of pain, impact of pain on sleep), single functions (lifting/carrying, sitting, standing, walking) and individual comprehensive functions (daily self-care capability, social activities, travel).

#### Secondary outcomes

2.8.2

Autoimmune theory has been proposed as a factor responsible for immune events due to the special anatomical structure of the intervertebral disc. The existence of the nucleus pulposus as an isolation antigen, once exposed to the immune system, may be recognized as a non-self component, leading to stimulation of an immune response resulting in chronic inflammation, eventually resulting in lumbar and leg pain.^[19–21]^ Furthermore, studies have established that the elevated levels of IgG and IgM in serum are positively correlated with the severity of lumbago and leg pain.^[22]^ Therefore, IgG and IgM immune function measurements before and 3 weeks after treatment are important parameters for detection of treatment effects and adverse reactions during treatment and will be recorded.

### Complications and adverse events during and after treatment

2.9

All expected and unexpected adverse events will be recorded during practitioner contact time throughout the study. Adverse events related to FSN and acupuncture are commonly hematoma and syncope during treatment. All serious adverse events will be immediately reported to the study contact in order to further investigate the cause.

### Data management

2.10

After data collection is completed, all data will be recorded independently by two trained research assistants using paper case report forms (CRFs). Since, acupuncture and FSN are known to have minimal risk, a formal data monitoring committee is not required. Independent investigators employed by the hospital will regularly monitor and review the experimental data.

### Statistical analysis

2.11

Since FSN and acupuncture are known to have only minimal risk, implementation of additional safety precautions is not required. Sensitivity analysis will be conducted to determine the impact of incomplete records on the results. Missing data will not be estimated. Statistical analysis will be performed using R package v3.4.4 software. If a Shapiro–Wilk test indicates that the data are normally distributed, a *t* test is appropriate for calculation and comparison of differences between two groups, otherwise a Mann–Whitney *U* test is suitable. A *χ*^2^ or Fisher exact test is relevant for calculation of differences in count data.

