### Sample size calculation

2.4

In order to determine the number of participants required for each experimental group, the variability of results in a previously published article^[7]^ was used in the calculation. The main results of the two studies were obtained under similar circumstances. The sample size required for an unpaired *t* test was 60 individuals, including 32 in the FSN group and 28 in the acupuncture group. The calculation was performed using a significance level of .05 (i.e., 5% of type I errors, resulting in a 95% confidence interval) and an absolute error of 5%. Considering a dropout rate of 10%, 80 patients are required to generate 80% of the power, at a significance level of .05.^[15]^

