##### VAS^[16]^

2.8.1.1

Patients were marked on a 100-mm visual analogue scale prior to and 3 weeks following treatment for assessment of their pain level (from no pain to very severe), which was then recorded by the evaluator.

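### Section 2.11 fixes an unadjusted t or Mann-Whitney test chosen by a normality pretest, with no stated role for baseline and no single effect measure

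*Protocol article*

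**What the plan says.** Section 2.11 (Statistical analysis) gives one rule for comparing continuous outcomes between the groups. "If a Shapiro–Wilk test indicates that the data are normally distributed", a t "test is appropriate for calculation and comparison of differences between two groups". Failing that, a Mann-Whitney U "test is suitable". The section names no covariate, adjusted model, change score or effect estimate. It does not say which data go into the Shapiro-Wilk test (each arm, both pooled, or residuals) or at what level.

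Baseline is recorded for all three primary outcomes:

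- VAS (2.8.1.1): "prior to and 3 weeks following treatment for assessment of their pain level".
- JOA (2.8.1.2): "All scores before and 3 weeks after treatment were recorded and total scores calculated".
- ODI (2.8.1.3): "Prior to and 3 weeks following treatment, the Oswestry disability index (ODI) of each patient was recorded".

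Section 2.8.2 does the same for IgG and IgM.

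Section 2.4 sizes the trial for an unpaired t test: "The calculation was performed using a significance level of .05", and "Considering a dropout rate of 10%, 80 patients are required to generate 80% of the power". Section 2.5 allocates the 80 patients 1:1.

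**The concern.** There are two linked weaknesses in the stated rule.

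First, a two-sample test without a baseline covariate leaves explainable between-patient variation in the error term, and chance baseline differences between two arms of 40 stay in the estimate. The scores that would remove much of this are already being collected.

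Second, the trial's own data choose the test. A t test goes with a difference in means and a Mann-Whitney test with a comparison of ranks. VAS could be reported one way and ODI or JOA the other, for no reason fixed in advance. Because the input and level of the pretest are not given, two analysts could follow the section faithfully and reach different tests.

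What is at stake is precision in a trial of 80 patients and a clearly defined result for each primary outcome. The validity of the comparison is not in question.

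**Working it through.** **Inputs.** From the protocol: significance level 0.05 (taken as two-sided, since the side is not stated), 80% power, 80 patients, 10% dropout, 1:1 allocation. This gives 80 × 0.9 / 2 = 36 analysed per arm. Not in the protocol: the correlation r between baseline and 3-week score, assumed to lie between 0.3 and 0.7, and the effect size.

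**The plan's own figure.** The 60 patients (32 + 28) cannot be rebuilt, because section 2.4 gives neither a difference nor a standard deviation. Solving backwards, 32 v 28 with 80% power corresponds to a standardised difference d of 0.737 (t test). The step from 60 to 80 does not follow from 10% dropout either (60 / 0.9 = 67). That is a separate matter and does not affect this point.

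**Variance of the group difference.** Assume the same standard deviation σ at both times and in both arms, and a linear relation. The per-patient variances are σ² for the final score, 2(1 − r)σ² for change, and (1 − r²)σ² for ANCOVA. Hence ANCOVA/final = 1 − r², and ANCOVA/change = (1 − r²) / [2(1 − r)] = (1 + r)/2.

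| r | ANCOVA/final | cut | ANCOVA/change | cut |
|---|---|---|---|---|
| 0.3 | 0.91 | 9% | 0.65 | 35% |
| 0.5 | 0.75 | 25% | 0.75 | 25% |
| 0.7 | 0.51 | 49% | 0.85 | 15% |

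ANCOVA has the smaller variance in every cell. Below r = 0.5, change scores are worse than using the final score alone.

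**Power at 36 per arm.** Power = Φ(d / (k√(2/36)) − 1.96), with k = 1 for the final score and k = √(1 − r²) for ANCOVA. Take the effect that has 80% power on final scores: d / √(2/36) = 1.960 + 0.842 = 2.802, so d is about 0.66 (0.67 with the t distribution).

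- r = 0.3: 2.802 / 0.954 = 2.937; Φ(0.977) = 0.84
- r = 0.5: 2.802 / 0.866 = 3.235; Φ(1.275) = 0.90
- r = 0.7: 2.802 / 0.714 = 3.923; Φ(1.963) = 0.975

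With the back-solved d = 0.737 instead, power is 87.9% on final scores and 90.6 / 95.1 / 99.2% with ANCOVA. The gain therefore runs from about 3 points to about 17, depending on r and d.

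**The pretest, by simulation** (36 per arm, Shapiro-Wilk at 0.05 in each arm, Mann-Whitney if either arm rejects; the level and the data tested are assumptions).

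- *Type I error* of the two-stage rule was 4.9% to 5.4% over normal, floor-clipped and two skewed distributions (10,000 runs each), against 4.8% to 5.2% for the t test alone.
- *Power* with a VAS clipped at 0 (latent means 30 v 17, SD 20) was 0.752 for the t test, 0.744 for Mann-Whitney and 0.750 for the two-stage rule.
- *How often Mann-Whitney is chosen* depends on the distribution. For truly normal data it is about 10% per outcome, so 1 − (1 − 0.1013)³ = 27% for at least one of three outcomes if they were independent. For VAS-like data clipped at 0 with SD 20, it is about 88% at latent means 30 v 17, 59% at 25 v 25, 27% at 30 v 30, and 7% to 9% at means of 37 to 50.

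**The case against.** The strongest objection is that this is a condensed article. Covariates and the exact analysis variable are often left to a full protocol or analysis plan, and an unadjusted two-sample test in a randomised trial is valid. The second part is right: nothing here makes the planned comparison biased. The first part does not remove the point, because section 2.11 does not leave the method open. It states a rule, and the criticism is of that rule.

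A reader might infer that the plan throws the baseline scores away. The text does not establish this. It does not say whether the 3-week score or the change is tested, and a test on changes would use baseline, though less efficiently. What can be said is that baseline has no stated role.

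A reader might also infer that the pretest inflates false positives, costs power, or will usually fail because VAS ends near zero. The simulations show no material effect on error rate or power. The protocol gives no expected post-treatment VAS, and the rejection rate moves from under 10% to almost 90% with the assumed mean. The t and Mann-Whitney tests do disagree on significance in about 5% of simulated trials under an effect, but the same occurs when the floor barely acts, so it is no evidence of a floor problem. Only VAS-like floors were simulated, not JOA, ODI or the immunoglobulins.

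Nor does a rank test rule out an estimate in mm or points, since a Hodges-Lehmann shift can accompany it. The fair criticism is that section 2.11 names no estimate at all.

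Finally, the Introduction describes the aim as feasibility and preliminary results. That lowers the stakes, but section 2.4 still sizes the trial for a powered comparison.

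**Conclusion.** The point holds as a matter of efficiency and clear reporting, and the change should be made. As written, the analysis is less precise than baseline adjustment across the whole assumed range of r, whichever variable is tested. The power gain is modest at r = 0.3 and large at r = 0.7. These sizes rest on an assumed correlation, equal variances at the two times, and an effect size that the protocol does not state; the direction does not depend on the effect size.

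The pretest is a lesser fault. It leaves the form of the result to the data and allows it to differ among three primary outcomes. How often that would happen cannot be known from the protocol.

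**What to change.** In section 2.11, for each continuous outcome (VAS, JOA, ODI, IgG, IgM):

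1. Prespecify one model, a linear regression of the 3-week score on group and that outcome's own baseline (ANCOVA).
2. Report the adjusted mean difference with its 95% confidence interval, using robust or bootstrap standard errors if the data are skewed.
3. Remove the Shapiro-Wilk test as a means of choosing the analysis.
4. Keep the Mann-Whitney test, with a Hodges-Lehmann shift and its interval, as a sensitivity analysis only.

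The cost is a change of wording and a few lines of code in R, which section 2.11 already names. No new data, visits or patients are needed. The change should be made before anyone sees outcome data by group.

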### Ethics and dissemination

2.12

Patients and the public were not involved in the design of this study. The participants will be informed of the result of this study during the follow-up visit. Besides, we will enlist their help in disseminating the research findings.

## Results

3

The results of this trial will be published on the website of the China Clinical Trial Registration Center and in peer-reviewed journals or academic conferences.

## Discussion

4

It has been established that conservative treatment, especially FSN, is effective in relieving LDH pain symptoms and promoting functional recovery. In the era of opioid abuse and excessive use of non-steroidal anti-inflammatory drugs to relieve lumbago and leg pain symptoms, floating needle therapy has good prospects for the non-surgical relief of such patient incapacity. At present, the theory explaining the analgesic mechanisms of floating needle treatments are thought to mainly involve loose connective tissues^[23]^ with special structures representing the material basis for its effectiveness. Subcutaneous loose connective tissues in a liquid crystal state exhibit piezoelectric and anti-piezoelectric effects. When floating needles are used, especially when performing a sweeping action, the spatial configuration of the loose connective tissue in its liquid crystal state changes and bioelectricity is released. Loose connective tissue has excellent conductivity and can conduct bioelectricity with high efficiency. When the bioelectricity reaches an MTrP, it produces an anti-piezoelectric effect, changes cellular ion channel, mobilizes the internal disease resistance mechanisms, thus relieving pain rapidly. There is also a doubtful nerve theory,^[24]^ which suggests that FSN therapeutics stimulate pain-transmitting nerves, which can block the conduction of pain-sensing fibers in those nerves and inhibit the nociceptive stimulation reaction of spinal dorsal horn cells, thus achieving an analgesic effect.

There are a number of limitations to the present study. Firstly, there may be differences in patient gender, age, lumbar spine segments manifesting disease, prominence, etc, so sub-group analysis may be required to judge the effectiveness of FSN for different sub-groups. Secondly, because VAS, JOA Score, ODI, and other indicators are subjective, the educational level of patients and their cognitive ability may influence the results, biasing the outcome indicators. Finally, this study was conducted in China, and the subjects were mostly Chinese. Whether FSN is effective for other races requires confirmation using a multi-center study in the future.
